### Inclusion and exclusion criteria (Aim 2)

Inclusion criteria are fee-for-service Medicare enrollment for at least 12 consecutive month and 12 months FFS with Part A, B, and D enrollment following the index date for at least 12 months or until death, and presence of atrial fibrillation as defined in the exposure section. The index date for patients exposed to anticoagulation will be the date of the first anticoagulant prescription drug claim occurring after the diagnosis of AF. For potential controls, only patients with no exposure to anticoagulation throughout the study period would be eligible to avoid selecting controls who start an anticoagulant during the follow-up period. For controls, inclusion and exclusion criteria will be examined for each year after AF diagnosis, and the midpoint of one random year will be selected as the index date for each control patient.

Exclusion criteria include:

Patients with any claim for CRAO in the 12 months prior to AF diagnosis or index date for controls;Patients who die within first 12 months of enrollment;Patients taking therapeutic-dose heparin, enoxaparin, dalteparin, fondaparinux, or betrixaban.

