### Exposure

The primary exposure of interest is prevalent atrial fibrillation/atrial flutter. Atrial fibrillation/atrial flutter will be defined through ICD-9-CM 427.13 or ICD-10-CM code I48 in 2 outpatient claims or one inpatient claim within 365 days [16–18]. Episodes of atrial fibrillation within 1 month of inpatient surgery will be excluded to avoid including patients with isolated post-operative atrial fibrillation [19].

The secondary exposure of interest (among patients with atrial fibrillation) is exposure to anticoagulation. For our secondary analysis (Objective 2), we will utilize Medicare Part D prescription drug claims to identify patients taking a direct acting oral anticoagulant (DOAC) or warfarin.

A list of search terms to identify anticoagulant drugs will be utilized as per Table 1, below:

**Table 1 pone.0296251.t001:** Drug lookup queries for anticoagulant exposure.

Drug Name	
Warfarin	Part D claim for generic drug name like ‘%WARFARIN%’, summarized per month (90-day fills will be imputed to monthly indicators)
Apixaban	Part D claim for generic drug name like ‘%APIXABAN%’, summarized per month (90-day fills will be imputed to monthly indicators)
Dabigatran	Part D claim for generic drug name like ‘%DABIGATRAN%’, summarized per month (90-day fills will be imputed to monthly indicators)
Edoxaban	Part D claim for generic drug name like ‘%EDOXABAN%’, summarized per month (90-day fills will be imputed to monthly indicators)
Rivaroxaban	Part D claim for generic drug name like ‘%RIVAROXABAN%’, summarized per month (90-day fills will be imputed to monthly indicators)

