### Adjustment covariates

We will utilize the following pre-specified covariates for risk adjustment: age, biological sex, race/ethnicity, and cardiovascular comorbidities and medical risk factors, including the medical comorbidities included in the Charlson Comorbidity Index (except for cardiac arrhythmias, which subsumes our primary exposure of interest), and additionally including hypertension, hyperlipidemia, valvular heart disease, and smoking status, using validated ICD-9-CM and ICD-10-CM algorithms [20–23]. Carotid stenosis and Stroke/TIA are contained in the cerebrovascular disease group of the Charlson Comorbidity Index. S1 and S2 Figs show the directional acyclic graphs representing our understanding of possible confounding variables.

We will ascertain comorbidities using a twelve-month look-back period from the patient’s index date (July 1 of initial year of inclusion in cohort for controls) using established claims-based algorithms. These are outlined in Table 2, below.

**Table 2 pone.0296251.t002:** List of international classification of diseases codes used for comorbidity adjustment.

Comorbidity	ICD-9 Code	ICD-10 Code	Citation
Hypertension	401.*, 402.*, 403.*, 404.*, 405.*, 437.2*	I10.*-I13.*, I15.0, I15.2, I15.8, I15.9, I16.*, I67.4*	Birman-Deych, 2005 [21]
Hyperlipidemia†	272.x	E78.x	Oake, 2017 [22]
Tobacco Use††	305.1, 649.0x, 989.84, V15.82; CPT codes 99406, 99407, G0436, G0437, G9016, S9453, S4995, G9276, G9458, 1034 F 4004 F 4001 F	F17.x, T65.2xx, Z87.891, CPT codes 99406, 99407, G0436, G0437, G9016, S9453, S4995, G9276, G9458, 1034 F 4004 F 4001 F	Desai, 2016 [23]
Valvular Heart Disease	394.*, 395.*, 396.*, 397.*, 398.9*, V42.2*, V43.3*, 424.*	I05.*-I08.*, I09.1*, I09.81, I09.89, I09.9*, I34.*-I39.*, Z95.2*, Z95.3*, Z95.4*	Birman-Deych, 2005 [21]

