### Statistical analysis plan

#### Re-estimation of propensity scores and overlap weighting

To adjust for the observed confounding and focus on the patient population in clinical equipoise, we will first re-estimate the propensity scores in the matched sample and then apply propensity score overlap weighting [25–27] to ensure exact balance of baseline covariates between patients with and without AF.

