#### Regression modeling (aim 2)

a) In keeping with target trial emulation methodology as described above, the index date for patients exposed to anticoagulation will be the date of the first anticoagulant prescription drug claim occurring after the diagnosis of AF. For potential controls, only patients with no exposure to anticoagulation throughout the study period would be eligible to avoid selecting controls who start an anticoagulant during the follow-up period. For controls, inclusion and exclusion criteria will be examined for each year after AF diagnosis, and the midpoint of one random year will be selected as the index date for each control patient.b) Similar to Aim 1, patients diagnosed with CRAO precedent to or concurrent to AF diagnosis will be excluded and these patients will be examined in an exploratory analysis.c) Our primary analysis will utilize propensity score overlap weighting methodology to approximate a randomized design where baseline hazard of CRAO of patients receiving anticoagulation vs. not receiving is comparable. We will incorporate the following variables to define the propensity score: age, time since first AF claim, sex, geography, race, Medicaid dual eligibility, vascular comorbidities and non-vascular comorbidities relevant to the likelihood that a patient will be treated with anticoagulation (to include all of the comorbidity variables included for Aim 1 propensity score, as well as history of gastrointestinal bleeding or peptic ulcer disease (using validated ICD-9-CM codes 531.x (gastric ulcer), 532.x (duodenal ulcer), and 578.x (gastrointestinal hemorrhage) and their ICD-10-CM counterparts K25.x, K26.x, and K92.2) and history of intracranial hemorrhage (any of ICD-10-CM I60, I61, S06.3, S06.4, S06.5, S06.6 and their ICD-9-CM counterparts 430.x, 431.x, 432.x)) [32–35].d) Our principal effect of interest is the hazard of CRAO among patients treated with any oral anticoagulant agent compared to those not treated. Given variable patient adherence to anticoagulation, we will take advantage of the strength of Part D data (which records pharmaceutical fills rather than prescriptions) and treat anticoagulation exposure as a time-varying covariate for patients exposed to anticoagulation.e) We will perform identical sensitivity analyses as described in Aim 1.f) Table shells for the results of Aim 2 are shown in Table 8.

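### The Aim 2 propensity score does not separate competing reasons to anticoagulate (venous thromboembolism, prosthetic valve, mitral disease), which leaves residual confounding by indication

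*Protocol article*

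**What the plan says.** - **Treated arm.** The Aim 2 inclusion criteria set the index date at the "date of the first anticoagulant prescription drug claim occurring after the diagnosis of AF", and Regression modeling (aim 2), item a, repeats the rule. The Exposure section uses Part D claims to "identify patients taking a direct acting oral anticoagulant (DOAC) or warfarin", and Table 1 searches on generic drug name. The reason for the fill is not used.
- **Controls.** The same section states that "only patients with no exposure to anticoagulation throughout the study period would be eligible".
- **Exclusions.** These are prior CRAO, death in the first 12 months, and "Patients taking therapeutic-dose heparin, enoxaparin, dalteparin, fondaparinux, or betrixaban". None concerns another indication for an oral anticoagulant.
- **Propensity score.** Regression modeling (aim 2), item c, lists demographic and AF-duration terms and comorbidities, "to include all of the comorbidity variables included for Aim 1 propensity score". It adds gastrointestinal bleeding or ulcer and intracranial hemorrhage.
- **Valve covariate.** Table 2 has one Valvular Heart Disease row. Its ICD-9 codes are "394.*, 395.*, 396.*, 397.*, 398.9*, V42.2*, V43.3*, 424" (all subcodes). Its ICD-10 codes run over I05-I08, parts of I09, I34-I39 and Z95.2-Z95.4. Valve-replacement status (V42.2, V43.3, Z95.2-Z95.4) and rheumatic mitral codes (394, I05) therefore sit in the same flag as other native valve disease (424, I34-I39).
- **Venous thromboembolism.** No deep vein thrombosis or pulmonary embolism code appears in Table 2 or in the Aim 2 additions.

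**The concern.** The two entry rules act together. An AF patient who starts warfarin or a DOAC for a valve replacement or a venous thrombosis, even years after the AF diagnosis, enters the treated arm at that fill and can never be a control. The conditions that named the Aim 2 additions to the score (bleeding, ulcer, intracranial hemorrhage) are reasons not to treat. Competing reasons to treat were not added.

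A score can balance only what it contains. Venous thromboembolism is absent, so it stays unbalanced except through correlation with other covariates. The valve flag is balanced as a whole, but within it the treated patients can hold more replaced valves and mitral disease than the untreated. If those patients have a higher CRAO hazard, the treated arm carries extra hazard unrelated to the effect of anticoagulation, and the hazard ratio moves upward. Aim 2 looks for a protective effect on a rare outcome, so this direction could hide a benefit.

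**Working it through.** The plan gives no figure for Aim 2. Its only design figure, the Aim 1 power, does not bear on this point. The check is therefore an illustration. The one input from the documents is the 50-60% treated share in the Introduction, which refers to patients meeting guideline criteria. Every other input is assumed.

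**A. Indication missing from the score (the position of venous thromboembolism)**

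Inputs: overall treated share P = 0.5 or 0.6. Share of AF patients with the indication q = 0.02 to 0.10 (assumed). Probability that they are treated t = 0.90 to 0.99 (assumed). CRAO hazard multiple g = 1.5 to 3 (assumed). No other covariate predicts the indication.

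- Share of the treated arm: s1 = q·t/P. Lowest: 0.02 × 0.90 / 0.6 = 3.0%. Highest: 0.10 × 0.99 / 0.5 = 19.8%.
- Share of controls: s0 = q(1−t)/(1−P). Lowest: 0.02 × 0.01 / 0.5 = 0.04%. Highest: 0.10 × 0.10 / 0.4 = 2.5%.
- Bias factor on the HR: [1 + s1(g−1)] / [1 + s0(g−1)].
  - Low end (P = 0.6, q = 0.02, t = 0.90, g = 1.5): s0 = 0.02 × 0.10 / 0.4 = 0.5%, and 1.015 / 1.0025 = 1.01.
  - High end (P = 0.5, q = 0.10, t = 0.99, g = 3): s0 = 0.10 × 0.01 / 0.5 = 0.2%, and 1.396 / 1.004 = 1.39.
- With its own score term, the indication has the same weighted share in both arms, between 0.08% and 3.9% over this grid, and this source of bias disappears.

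**B. Indication inside a pooled flag (the position of prosthetic valve and mitral disease)**

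Inputs, all assumed: 25% of AF patients carry the flag. A share v = 5% or 20% of those has a prosthetic valve or mitral stenosis. In that subgroup 95% are treated, and 55% of everyone else. The hazard multiple is 2 to 5. Overlap weights are 1 − e for treated patients and e for controls, where e is the propensity score.

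- Score in flagged patients: 0.05 × 0.95 + 0.95 × 0.55 = 0.57 for v = 5%, and 0.63 for v = 20%. Unflagged: 0.55.
- Total weight in each arm: 0.25 × 0.57 × 0.43 + 0.75 × 0.55 × 0.45 = 0.2469 for v = 5%, and 0.25 × 0.63 × 0.37 + 0.1856 = 0.2439 for v = 20%.
- Subgroup in the weighted treated arm: 0.0125 × 0.95 × 0.43 / 0.2469 = 2.1%, and 0.05 × 0.95 × 0.37 / 0.2439 = 7.2%.
- Subgroup in the weighted controls: 0.0125 × 0.05 × 0.57 / 0.2469 = 0.14%, and 0.05 × 0.05 × 0.63 / 0.2439 = 0.65%.
- Bias factor: low end (v = 5%, multiple 2) 1.0207 / 1.0014 = 1.02. High end (v = 20%, multiple 5) 1.2882 / 1.0258 = 1.26. At the high end a true HR of 0.70 would read 0.70 × 1.26 = 0.88.
- With a separate term, the subgroup's share is the same in both arms: 0.0125 × 0.0475 / 0.2450 = 0.24%, and 0.05 × 0.0475 / 0.2375 = 1.0%.

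Both illustrations count all treated-arm time as exposed, so they overstate the bias where courses are short.

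**The case against.** Much of the case on the other side stands.

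- **Valves are adjusted for in part.** Their codes enter the Aim 2 score through the Aim 1 comorbidities. It would be wrong to say that weighting does nothing. Illustration B shows what the pooled flag leaves behind.
- **Exposure is time-varying.** Item d uses monthly fill indicators, so a short course adds only its filled months to exposed time. This limits the effect of brief venous-thrombosis or post-operative courses. It helps much less for a long-term indication such as a prosthetic valve.
- **Venous thromboembolism confounds only if it also affects CRAO hazard.** The documents do not establish that. With a hazard multiple of 1 there is no bias from this source.
- **Control endpoints exist.** A large embolic bias should also weaken the ischemic stroke result, which Limitations plans to compare with trial evidence. That could signal a large distortion. It would not reveal a modest one, identify the cause or correct the CRAO estimate. Urinary tract infection is not an embolic outcome and need not respond.

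A reader might also infer more than the text supports:

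- **That these treated patients have no valid untreated comparator.** The documents give no treatment rates by indication, so at most local non-positivity is possible.
- **That Aim 2 claims equipoise.** The phrase "focus on the patient population in clinical equipoise" belongs to a sentence about patients with and without AF, which is Aim 1.
- **That Aim 2 asks only about anticoagulation prescribed for AF.** Aims and item d ask about any oral anticoagulant use among AF patients, so exclusion is not required by the stated question.
- **That a true HR of 0.70 could read 0.98.** This needs an unweighted 10% share in the treated arm, none in controls and a fivefold hazard all at once: 0.70 × (1 + 0.10 × 4) = 0.98.

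**Conclusion.** The point holds as residual confounding by indication in Aim 2, with possible local non-positivity. The documents show its source: fills identified by drug name, controls who are never exposed, no venous thromboembolism covariate, and one valve flag that mixes embolic and other valve disease. They do not show its size. Under the assumed inputs, the HR is inflated by a factor of 1.01 to 1.39 for an indication absent from the score, and by 1.02 to 1.26 for one hidden in the pooled valve flag. The upward direction rests on the assumption that the indication raises CRAO hazard. That is most plausible for embolic valve disease and open for venous thromboembolism. Nothing here affects Aim 1 or its power calculation. The point does not invalidate Aim 2, but the gap is avoidable and should be closed before the analysis.

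**What to change.** In Regression modeling (aim 2), item c:

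1. Split the Table 2 valve row into two score terms: prosthetic valve or mitral stenosis, using the relevant subset of the existing codes, and all other valve disease.
2. Add a score term for a deep vein thrombosis or pulmonary embolism claim in the 12-month look-back to the index date.
3. Add a sensitivity analysis that excludes patients with either indication, applied identically in both arms, and report it beside the primary result in Table 8.

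The primary cohort and the stated question stay as they are. Mandatory exclusion is a defensible alternative but a debatable design choice, and the documents do not require it. The plan already takes a similar step for left atrial appendage occlusion, described in Limitations as an exclusion sensitivity analysis.

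Cost: a few code lists applied to claims already held, one extra model run, and a somewhat smaller sample in the sensitivity analysis only.

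### Aim 2 sets time zero by different rules for treated patients and controls, so patients who start anticoagulation soon after AF diagnosis have few or no controls at the same time since diagnosis

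*Protocol article*

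**What the plan says.** The protocol article gives the rule twice, under Inclusion and exclusion criteria (Aim 2) and in item a) of Regression modeling (aim 2).

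- **Treated patients:** time zero is "the date of the first anticoagulant prescription drug claim occurring after the diagnosis of AF".
- **Controls, who may enter:** "only patients with no exposure to anticoagulation throughout the study period would be eligible".
- **Controls, time zero:** "For controls, inclusion and exclusion criteria will be examined for each year after AF diagnosis", and then "the midpoint of one random year will be selected as the index date for each control patient". The text does not say whether a year runs from diagnosis or is a calendar year, or whether the year of diagnosis counts.

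Item a) presents this rule as target trial emulation. Item c) adds: "Our primary analysis will utilize propensity score overlap weighting methodology to approximate a randomized design". The propensity score variables begin with "age, time since first AF claim, sex, geography, race, Medicaid dual eligibility"; no functional form is given for time. Item d) defines the effect of interest as treatment with any oral anticoagulant against none, with no restriction on when treatment starts. The CRAO washout in the Aim 2 exclusion criteria is tied to AF diagnosis for treated patients and to the index date for controls.

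**The concern.** In a target trial both arms start at the same point in the course of the disease. Here a treated patient can start the day after AF diagnosis, while on the two most natural readings a control cannot start until about 6 months after it. Early initiators are then compared with patients at a later stage. The Limitations section names the careful choice of index date and controls as a main safeguard of Aim 2, so a weakness in that rule matters.

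Two things are at stake. If the CRAO hazard is raised soon after AF diagnosis, that excess is observed mainly or only in the treated group, and anticoagulation would look less protective than it is. If the weighting instead removes the early initiators, the result applies to a narrower group than item d) describes, and the protocol does not say so.

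**Working it through.** The protocol gives no Aim 2 figure to reproduce. It also gives neither the distribution of time from AF diagnosis to first fill nor the CRAO hazard by time since diagnosis. Both are assumed below.

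**Step 1. Earliest control index date.** Let k = 0, 1, 2, … be the chosen year and d the fraction of the calendar year elapsed at diagnosis.

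- Reading A, years from diagnosis: 12(k + 0.5) = 6, 18, 30, … months. Minimum 6.
- Reading B, July 1 of calendar years after the diagnosis year: 12(1 − d + k + 0.5). Minimum 6, and 6 to 18 months for the first such year.
- Reading C, July 1 with the diagnosis year included: 12(0.5 − d) for those diagnosed before July 1. Minimum about 0. For later diagnoses that July 1 precedes AF, so the next one is used.

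For treated patients the minimum is about 0 on every reading.

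**Step 2. What overlap weighting does.** Treated patients get weight 1 − e and controls e, where e is the fitted propensity score. The logistic score equations give, for each term x in the model,

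Σ over treated (1 − e)x = Σ over controls e·x.

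The weighted means of the terms in the model are therefore equal. Other features of the distribution need not be. Now let x be an indicator for under 6 months. On readings A and B the right-hand side is 0, so the early initiators' total weight must be 0. Either such a term is in the model and early initiators are excluded, or it is not and they can keep weight that no control matches.

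**Step 3. Share of weight under 6 months (simulation, 200,000 per group).**

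*Assumption set 1:* 40–60% of initiators start early (exponential, mean 1–3 months), the rest with mean 24 months; controls have 1 to 10 eligible years. This puts 48–69% of initiators under 6 months. Results on reading A, treated v control:

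- linear term: 38–53% v 0%, with identical weighted mean times
- quadratic term: 32–44% v 0%
- adding a log term: about a fifth v 0%
- 6-month bins: 0% v 0%

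*Assumption set 2:* 30%, 50% or 70% start early (mean 1 month), the rest with mean 18 months; controls have 1 to 8 eligible years. This puts 50%, 64% and 78% of initiators under 6 months.

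| Reading | Controls under 6 months, unweighted | Linear term, treated v control | 6-month bins, treated v control |
|---|---|---|---|
| A | 0% | 38–60% v 0% | 0% v 0% |
| B | 0% | 32–50% v 0% | 0% v 0% |
| C | about 17% | 39–61% v 25–34% | equal |

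**Step 4. Rate ratio with no drug effect.** Suppose the CRAO hazard is m-fold in the first 6 months after diagnosis. On reading A no control is exposed to that excess. Over H months from index, ignoring losses, the ratio is 1 + (m − 1)E/H, where E is the weighted mean number of early months still ahead of a treated patient. Set 1 with a linear term gives E of about 1.3–2.5 months.

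| Early hazard (assumed) | First year | Three years |
|---|---|---|
| no excess | 1.00 | 1.00 |
| 1.5-fold | 1.06–1.10 | 1.02–1.04 |
| 2-fold | 1.11–1.21 | 1.04–1.07 |
| 3-fold | 1.23–1.42 | 1.08–1.14 |

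For the 2-fold row: 1 + 1.3/12 = 1.11 and 1 + 2.5/12 = 1.21. With the log term added, the 2-fold first-year ratio falls to about 1.04; with bins it is 1.00. On reading C with a linear term, the 2-fold ratios are 1.06–1.14 over one year and 1.02–1.05 over three.

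**The case against.** The strongest reply is that time since first AF claim is already in the propensity score. Its functional form is a detail that an analysis plan may settle, and overlap weighting is meant to discount patients who have no counterpart. With binned time the bias from this source disappears on readings A and B. This stands. A reader might infer that the weighting cannot make the groups comparable at all, but the protocol does not support that: it can do so for patients who start later. It cannot do so for early initiators, because removing their imbalance means removing them.

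Four further points also carry weight.

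- **The 6-month gap is not fixed by the text.** Aim 1 uses July 1 of each calendar year. If Aim 2 does the same and counts the diagnosis year, some controls start within 6 months. The gap is then only partial, although the groups still start at different times.
- **The time variables differ.** The score counts from the first AF claim, whereas diagnosis may be the second outpatient claim, up to 365 days later. Some prompt initiators therefore share score values with controls. The simulation ignores this.
- **The ratios rest on assumed inputs.** They also compare fixed groups, whereas item d) treats exposure as time-varying among the treated.
- **Immortal time.** A reader might infer that controls' months before index count as event-free follow-up. Nothing in the protocol says so; both groups must be alive at their own index date.

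**Conclusion.** The point holds in a limited form. The stated index-date rules differ between the groups, and on the two most natural readings of "For controls, inclusion and exclusion criteria will be examined for each year after AF diagnosis" no control starts within about 6 months of AF diagnosis. Early initiators then either keep weight that no control matches (38–53% v 0% with a linear time term, initiation timing assumed) or are largely or wholly weighted out. In the second case the estimate does not cover all patients treated with an oral anticoagulant. In neither case is the target-trial description met for early initiators.

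It would go too far to say that the Aim 2 hazard ratio will be biased towards harm. That needs an early excess CRAO hazard, which the protocol does not report, and a propensity model that leaves early initiators with weight. With no excess, the bias from this source is nil. With a doubled hazard, reading A and a linear term, it is about 1.11–1.21 over the first year and 1.04–1.07 over three. The rule should be corrected before the cohort is built.

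**What to change.** In Inclusion and exclusion criteria (Aim 2) and in item a) of Regression modeling (aim 2), replace the random mid-year rule. Give each eligible control an index date at an elapsed time since AF diagnosis drawn from the treated patients' distribution, or matched to one initiator's elapsed time. Apply every inclusion and exclusion criterion, including the CRAO washout, at that index date in both groups. Keep time since AF in the propensity score with a flexible form, and state whether it counts from the first AF claim or from the diagnosis date.

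The rule that controls are never anticoagulated can stay. If controls are instead drawn from all patients still untreated at that elapsed time, later initiators would enter as controls, and the protocol must say how their later treatment is handled.

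The cost is some extra cohort programming on the same data and the loss of controls who are not eligible at their assigned time.

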### Inclusion and exclusion criteria (Aim 1)

The inclusion criterion is continuous fee-for-service Medicare enrollment for at least 12 months prior to AF diagnosis or matched index date (July 1 of inclusion year) for controls and continuous enrollment in fee-for-service (FFS) Medicare after AF diagnosis/index date for at least 12 months or until death if death occurred before 12 months of continuous enrollment.

Patients with prevalent AF will be identified as follows:ICD-9-CM code 427.31 or ICD-10-CM code I48 in 2 outpatient claims or 1 inpatient claim within 365 days, in any diagnosis position of the claim [16–18]. The index date will be the date of the first qualifying inpatient claim or second qualifying outpatient claim. Patients will be required to have 12 months of FFS claims without an AF diagnosis prior to the index AF claims based on inclusion criteria.

Exclusion criteria are:

patients with any claim for CRAO in the 12 months prior to AF diagnosis or index date for controls (July 1 of potential inclusion year).

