### Outcome

The outcome of interest is incident central retinal artery occlusion. Central retinal artery occlusion will be identified through ICD-9-CM 362.31, which we validated in a prior study [13] in the primary diagnosis position in any emergency department, inpatient, or outpatient claim. We will use the corresponding ICD-10-CM code H34.1x for claims occurring after September 31, 2015.

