### Analytical cohort

An analytic cohort will be generated by applying the below inclusion and exclusion criteria as follows:

All patients meeting the criteria for AF in the study period and meeting other inclusion/exclusion criteria will be identified as cases, and the date of AF diagnosis will serve as case’s index date for calculation of covariates. All remaining beneficiaries will be considered potential controls; inclusion and exclusion criteria will be applied based on an index date of July 1 for each year in the study period; all beneficiaries meeting inclusion/exclusion criteria for each year will be included in the potential control pool. For all potential controls with multiple index dates/years of eligibility, the year they contribute will be selected randomly. A multivariable logistic regression analysis will be conducted using cases and potential controls to create propensity scores for AF status; the final control group will be selected using propensity score matching to the AF cases.

Survival time for patients will be defined as the number of months from the index date when criteria were met. Patients will be censored at death, at the end of fee-for-service enrollment, or at the end of data availability. When 85% of the cohort has died or been lost to follow-up, we will censor remaining patients at that point to avoid instability in estimates due to very small numbers of remaining participants.

Details of the cohort analysis will be reported using RECORD guidelines for analyses of routinely collected data, including use of a patient flow diagram [24].

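### Aim 2 closes the prior-CRAO exclusion at AF diagnosis for anticoagulated patients, although their follow-up starts at the first fill; controls are screened up to their own index date

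*Protocol article*

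**What the plan says.** Under Inclusion and exclusion criteria (Aim 2), the index date of an anticoagulated patient "will be the date of the first anticoagulant prescription drug claim occurring after the diagnosis of AF". For controls, "the midpoint of one random year will be selected as the index date for each control patient", and "For controls, inclusion and exclusion criteria will be examined for each year after AF diagnosis". The exclusion criterion in the same section removes "Patients with any claim for CRAO in the 12 months prior to AF diagnosis or index date for controls".

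Regression modeling (aim 2), item b, states the exclusion a second time and likens it to Aim 1: "patients diagnosed with CRAO precedent to or concurrent to AF diagnosis will be excluded". The Aim 1 criterion uses the same words as the Aim 2 criterion: "patients with any claim for CRAO in the 12 months prior to AF diagnosis or index date for controls".

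Two further rules decide which claims count. Under Analytical cohort, "Survival time for patients will be defined as the number of months from the index date when criteria were met". Under Outcome, CRAO is identified by its code "in the primary diagnosis position in any emergency department, inpatient, or outpatient claim".

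**The concern.** In Aim 1 the AF diagnosis date is the index date, so a look-back that ends there is sound. Aim 2 keeps the same wording but moves time zero for treated patients to the first fill. Their look-back then ends before follow-up begins, and the interval in between is unscreened. For controls the look-back ends at time zero.

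A treated patient whose CRAO fell in that interval enters as if free of it. The old claim is not counted, because time starts at the fill. A later primary-position claim for the same occlusion, such as an outpatient eye visit, meets the outcome definition. Such visits cluster soon after the occlusion and so, for a recent CRAO, soon after the fill, when the time-varying exposure is most likely to be switched on.

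This affects the principal Aim 2 comparison. Extra events in the treated arm raise the hazard ratio and could mask a protective effect. If a CRAO in an untreated AF patient is sometimes the reason for the first fill, the interval holds more CRAO than the background rate predicts.

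**Working it through.** The protocol gives no Aim 2 figure to reproduce, so the check compares the windows first and then illustrates the size.

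**Windows, by arm**

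| | Treated | Control |
|---|---|---|
| Time zero | First fill after AF diagnosis | Midpoint of a random eligible year after AF diagnosis |
| 12-month look-back ends at | AF diagnosis | Own index date |
| CRAO after AF diagnosis, within 12 months before time zero | Kept | Excluded |
| CRAO after AF diagnosis, more than 12 months before time zero | Kept | Kept |
| CRAO in the 12 months before AF diagnosis | Excluded | Excluded by item b of the Aim 2 regression section |

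The arms therefore differ in the third row, the year just before time zero.

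**Does another rule close the gap?**
- Item b of the Aim 2 regression section is also anchored at AF diagnosis, so it does not.
- The Outcome section states no washout that separates a follow-up claim from a new event.
- Prior CRAO is not among the Table 2 covariates, and the Table 2 footnote removes the transient retinal occlusion codes from cerebrovascular disease. The propensity score cannot balance it.
- Time since first AF claim is in the Aim 2 propensity score. That can equalise the length of the interval across arms, but it does not remove treated patients with a CRAO inside it.

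**Size (illustration)**

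Inputs:
- r = 22 per 100,000 per year, the rate assumed for AF patients under Sample size calculation.
- g = years from AF diagnosis to first fill (assumption). Only the part up to 1 year is differential.
- q = chance of a later primary-position claim for the same CRAO after the fill (assumption).
- F = years of follow-up (assumption).

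Per 100,000 treated patients, extra events = r × g × q. With no true effect, true events = r × F. The apparent hazard ratio is then about 1 + (g × q) / F, and r cancels.

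With q = 0.5:

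| g (years) | Extra events | F = 1 (22 true) | F = 3 (66 true) | F = 5 (110 true) |
|---|---|---|---|---|
| 0.5 | 22 × 0.5 × 0.5 = 5.5 | 1.25 | 1.08 | 1.05 |
| 1 | 22 × 1 × 0.5 = 11 | 1.50 | 1.17 | 1.10 |

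Wider limits:
- Smallest: g = 1 month, q = 0.25, F = 5 gives 22 × (1/12) × 0.25 = 0.46 extra events against 110, a ratio of 1.004.
- Largest: g = 1 year, q = 0.9, F = 1 gives 22 × 1 × 0.9 = 19.8 against 22, a ratio of 1.90.

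If CRAO prompts initiation, the interval rate among those who become treated exceeds r and the extra events rise in proportion.

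**The case against.** Several limits on the point are fair.

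**The gap is not confined to one arm.** A reader might infer that every CRAO before the first fill survives, and only among the treated. The documents do not support that. CRAO before or concurrent with AF diagnosis is excluded, and controls also keep a CRAO that falls after AF diagnosis but more than 12 months before their index date. The difference is limited to the year before time zero.

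**Larger inflation figures are tempting.** Setting 5.5 to 22 extra events against 55 gives 10 to 40%. But 55 is 5 years at 11 per 100,000, the rate the protocol assigns to people without AF. Using it for treated AF patients presumes that anticoagulation halves the risk. The upper end also needs a 2-year gap, whose second year is unscreened in controls too. Still larger figures need a high rate of CRAO-triggered initiation, for which the protocol offers no number.

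**Time-varying exposure softens the effect.** A repeat claim in a month without a fill would not count as exposed, whereas the arithmetic above assigns every extra event to treatment. This stands, although the first months after a first fill are mostly exposed.

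**The outcome is labelled incident.** An analyst might add a first-ever rule, but none is written, and the stated exclusion would contradict one for treated patients.

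**Aim 1.** A reader might infer that AF first coded during a CRAO encounter enters Aim 1 with an event on day 0. Item b of the Aim 2 regression section says that Aim 1 likewise excludes concurrent CRAO, and patients whose CRAO came before AF have a separate secondary analysis. What remains is a wording mismatch with the Aim 1 criterion.

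None of this screens the treated arm between AF diagnosis and first fill.

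**Conclusion.** The Aim 2 exclusion is wrong as written. It is tied to AF diagnosis for treated patients, whose time zero is the first fill, and the second statement of the rule repeats that anchor. The mechanism and the direction, against anticoagulation, follow from the text.

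The size does not follow from the text. About 5 to 10% extra treated events is a reasonable illustration under no true effect, a gap of 0.5 to 1 year, a 50% repeat-claim share, 5 years of follow-up and no CRAO-triggered initiation. None of these assumptions is documented. Shorter follow-up or triggered initiation makes the figure larger; prompt first fills or few repeat claims make it negligible.

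The protocol calls Aim 2 its secondary analysis, and the Aim 1 anchor is sound. The change should still be made before analysis, because the rule decides which events count in the main Aim 2 comparison and the bias has a known direction.

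**What to change.** - In both Aim 2 arms, exclude any CRAO claim in the 12 months up to and including the patient's own index date: the first fill for treated patients, the assigned index date for controls.
- Count outcomes only after that date.
- Reword item b of Regression modeling (aim 2) to use the same anchor and look-back.
- For consistency, extend the Aim 1 criterion to CRAO concurrent with AF diagnosis, as item b already implies.

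With the window re-anchored, the extra treated events from the year before the fill fall to zero in the illustration. A CRAO after AF diagnosis but more than 12 months before index would remain possible in both arms alike. Using all available history would catch more of these, but it is optional and gives patients look-backs of unequal length.

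The cost is a rewritten criterion, a small programming change and a small number of excluded patients.
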